#### 4.0 SELECTION AND ENROLLMENT OF SUBJECTS

##### 4.1 Inclusion Criteria for Study Entry (STEP I)

- 4.11 Children and youth  $\geq 4$  years to  $<25$  years of age at study entry.
- 4.12 HIV infection, defined as positive test results obtained from 2 different samples. Tests may include two of the same type OR two different types of tests listed below, as long as there are positive test results obtained from 2 different samples:
  - HIV-1 antibody (ELISA + WB), obtained at age  $>18$  months
  - HIV-1 culture, any age
  - HIV-1 DNA PCR, any age
  - HIV-1 RNA PCR  $>10,000$  copies/mL, any age
  - Neutralizable HIV-1 p24 antigen obtained  $>28$  days of age
- 4.13 In the opinion of the investigator, the route of HIV-1 transmission is perinatally acquired.
- 4.14 Subjects who are receiving ARVs must have been receiving a stable regimen for 90 days prior to entry with no intention to modify their regimen within 60 days following study entry.
- 4.15 Subjects who are not receiving ARVs at entry must not have received ARVs within 90 days prior to entry and must NOT plan to initiate ARVs within 60 days following study entry.

- 4.16 Ability to complete all study immunizations and evaluations, in the opinion of the investigator.
- 4.17 Females of child-bearing potential must have a negative pregnancy test within 72 hours prior to enrollment.

NOTE: “Female of child-bearing potential” is defined as girls who have reached menarche and have not undergone surgical sterilization (e.g., hysterectomy, or bilateral oophorectomy, or bilateral salpingotomy or tubal ligation). Acceptable documentation of lack of reproductive potential for females in this study is: lack of onset of puberty (by participant or care giver reported history or by physical examination), lack of menses (by participant or care giver reported history), or woman’s self-reported history of surgical sterilization.

- 4.18 Subjects (and/or their partners) who are participating in sexual activity that could lead to pregnancy must agree to use at least one of the following methods of contraception as long as they are in this study:
- hormonal birth control drugs (oral, injectable or transdermal)
  - male or female condoms with or without a spermicide
  - diaphragm/cervical cap with spermicide
  - intrauterine device (IUD).

Condoms are recommended because their appropriate use is the only contraception method effective for preventing HIV-1 transmission.

- 4.19 Subjects should have a documented platelet count of  $>50,000$  per  $\text{mm}^3$  and an ANC of  $>500$  per  $\text{mm}^3$  within the 30 days prior to study entry.
- 4.110 Youth of legal age ( $\geq 18$  to  $< 25$  years of age), parent or legal guardian, or subjects who are emancipated minors, who are willing and able to provide signed informed consent.

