4.3 Inclusion Criteria for STEP II

- 4.31 Received the first dose of **Influenza A (H1N1) 2009 monovalent study vaccine** at least 21 days ago.
- 4.32 Has a documented platelet count of  $>50,000$  per  $\text{mm}^3$  and an ANC of  $>500$  per  $\text{mm}^3$  within the 30 days prior to Step II entry.
- 4.33 Females of child-bearing potential must have a negative pregnancy test within 72 hours of Step II entry.

OR

If a woman became pregnant after Dose #1, she must be  $\geq 14$  weeks of gestation and have her obstetrician's permission to receive the vaccine.

NOTE: For management of women, who become pregnant after Dose #1, see section 6.7.

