Guillain-Barré syndrome (GBS) is an acute inflammatory neuropathy characterized by weakness, hyporeflexia or areflexia, and elevated protein concentrations in cerebrospinal fluid. Most persons who develop Guillain-Barré syndrome recover completely, although the recovery period may be as little as a few weeks or as long as a few years. About 30% of those with Guillain-Barré syndrome still have residual weakness after 3 years and about 3% may suffer a relapse of muscle weakness and tingling sensations many years after the initial attack. The rate of Guillain-Barré syndrome was significantly increased in individuals receiving the 1976 Swine Influenza (H1N1) vaccine at about 1 per 100,000 vaccine recipients. This has not been seen consistently with other influenza vaccines. Typically onset was within 6 weeks after vaccination. Interestingly, although vaccination rates have increased in the last 10 years, the numbers of reported cases of vaccine-associated Guillain-Barré syndrome have declined. It is unknown if the currently produced Novartis and other manufacturers, unadjuvanted and adjuvanted, **Influenza A (H1N1) 2009 monovalent vaccine** will result in the incidence of Guillain-Barré syndrome that was seen with the 1976 vaccine product as the mechanism leading to this response has not been completely elucidated.

There may be other unknown risks of participation. The risk to the fetus/infant is unknown because animal reproduction studies with the vaccine have not been conducted. There may be other unknown side effects.

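### The note to criterion 4.17 defines child-bearing potential by menarche but accepts an unqualified report of no menses as evidence against it, leaving it unclear who must have a pregnancy test before each dose

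*Combined protocol and SAP*

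**What the plan says.** Criterion 4.17 sets the entry rule: "Females of child-bearing potential must have a negative pregnancy test within 72 hours prior to enrollment". Its note then does two things.

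- It gives a definition. Child-bearing potential "is defined as girls who have reached menarche and have not undergone surgical sterilization". Current menstrual status plays no part in it.
- It gives a documentation list, opened by the words "Acceptable documentation of lack of reproductive potential for females in this study is". The list has three items. The first is that puberty has not begun, established from the history or on examination. The second, which is the one at issue, is "lack of menses (by participant or care giver reported history". The third is surgical sterilization on the woman's own account.

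For Step II, 4.33 reads "Females of child-bearing potential must have a negative pregnancy test within 72 hours of Step II entry", with a separate route for a woman who became pregnant after Dose #1. Appendix IA footnote 5 requires the test before each vaccination in girls of child-bearing potential. Neither place gives a definition of its own, so both depend on the 4.17 note.

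Under footnote 5, a positive Day 0 test bars enrolment and a positive Day 21 test defers Dose #2. Section 6.71 and Appendix IB then provide separate follow-up of mother and infant. On fetal risk, section 9.31 states: "The risk to the fetus/infant is unknown because animal reproduction studies with the vaccine have not been conducted".

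**The concern.** The definition turns on whether menarche has ever occurred. The documentation item turns on an absence of menses, with no wording such as never or not yet, no time limit, and no evidence needed beyond a report by the participant or caregiver. It applies to all females in a study that enrols up to, but not including, age 25 (4.11). In an adult, a reported lack of menses may simply mean that periods are absent now, and pregnancy is one reason for that.

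The documentation list is the part of the note that site staff apply, since it tells them what they may accept in place of a test. In a multi-center study, two sites could classify the same subject differently. If a site used the broad reading and the subject was pregnant without knowing it, she could be vaccinated untested. She would then miss the deferral in 6.35 and 6.71, the fetal heart rate check and the infant visit in Appendix IB, unless the pregnancy came to light in some other way.

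**Working it through.** There is no stated figure to reproduce and no arithmetic to do. The check sets the two sentences of the note side by side and classifies each kind of female subject under them. Reading A takes lack of menses to mean menarche not reached. Reading B takes it to mean no menses at present.

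| Subject | Definition | List, reading A | List, reading B |
|---|---|---|---|
| Puberty not begun | No potential | No potential (first item) | No potential (first item) |
| Puberty begun, never menstruated | No potential | No potential (second item) | No potential (second item) |
| Past menarche, not sterilized, has periods | Potential: test | No item applies: test | No item applies: test |
| Past menarche, not sterilized, no current periods | Potential: test | No item applies: test | **Second item applies: test may be omitted** |
| Surgically sterilized | No potential | No potential (third item) | No potential (third item) |

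The definition and the list agree in every row under reading A. Under reading B they disagree in one row only, the post-menarchal, non-sterilized subject without current periods. The text does not say which reading applies.

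**How far it carries.** 4.17 controls the test before Dose #1. 4.33 and footnote 5 control the test before Dose #2 through the same undefined-elsewhere term. The ambiguous row is therefore present at both doses.

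**What else would detect the pregnancy.**

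- Neither exclusion list (4.2 or 4.4) names pregnancy as an exclusion.
- Section 6.35 defers Dose #2 for pregnancy after Dose #1, but the pregnancy has to be known.
- Appendix IA schedules a history and physical examination at screening, Day 0, Day 21 and Step II Day 0. The contents listed in footnotes 2 and 3 do not name pregnancy or menstrual history.
- A pregnancy test is also marked for unscheduled visits, but those occur only for influenza-like illness, possible Guillain-Barré syndrome or possible adverse events.
- Criterion 4.18 requires contraception where sexual activity could lead to pregnancy. That lowers the chance of pregnancy and does not detect one.
- Criterion 4.214 leaves room for investigator judgment at entry.

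None of these reliably finds an unrecognised pregnancy.

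**The case against.** The best defence is that reading A is the natural one. The list comes straight after a menarche-based definition, and its items match that definition's two conditions: menarche not reached, or sterilization. Listing lack of menses apart from lack of puberty does not favour reading B, because a girl can enter puberty before she menstruates and both items are then needed. Caregiver report also fits a child who has not yet started. Moreover, the operative rules are tied to the defined term. Omitting the test in a post-menarchal, non-sterilized subject means letting a documentation item override the definition.

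All of that stands. It rules out a stronger conclusion that a reader might infer, namely that the note contradicts itself outright and permits such subjects to go untested. The contradiction exists only under reading B.

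A reader might also infer that the test is the only barrier. It is not: the safeguards listed in the check exist, and 6.71 covers a woman found to be pregnant before Dose #2 without limiting how this is found. Missing both tests would also require the broad reading to be applied twice. On severity, the fetal-risk statement in 9.31 has to be read with 6.71, which says that completing the series is important to the health of women who become pregnant after Dose #1.

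The defence does not remove the ambiguity. The item uses a different and broader word than the definition one sentence before it, and nothing in the text tells a site to take the narrow meaning.

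**Conclusion.** The point holds as an ambiguity in a safety check. The documentation item in 4.17 can be read in line with the definition, but its literal wording also covers a subject whom the definition requires to be tested. The ambiguity reaches the test before both doses, the main stated check for an unrecognised pregnancy.

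Its size cannot be stated. It is tempting to start from the at least 80 evaluable subjects planned in Groups 2 and 3 (40 + 40) and apply assumed proportions of females and of absent periods. The documents give neither proportion. Such a count would also include girls aged 9 and over who have not reached menarche and are properly exempt under either reading, and it would count omitted tests, not pregnancies.

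The conclusion assumes only that a site might apply the list as written. No endpoint, sample size, power or analysis is affected. It is a modest clarification that is worth making because it bears on subject safety and costs little.

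**What to change.** Reconcile the two sentences of the 4.17 note so that the definition and the documentation list describe the same condition. Using the definition's own menarche term in both places is one way to do it. Then have 4.33 and Appendix IA footnote 5 refer to that single definition. This aligns existing text and introduces no new clinical rule; the sponsor should confirm which meaning was intended.

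The cost is one phrase and two cross-references. With the menarche term in both places, the downside is a few additional urine pregnancy tests, at sites that had been using the broad reading. Sites already using the narrow reading would see no change.

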#### 4.2 Exclusion Criteria for Study Entry (STEP I)

- 4.21 Has a known allergy to eggs, **egg products, neomycin or polymyxin.**
- 4.22 Has a history, in the opinion of the site investigator, of severe reactions following previous immunization with seasonal influenza vaccines that would contraindicate receipt of any influenza vaccine.
- 4.23 Has a history of probable or proven pandemic **2009 H1N1 Influenza A** infection prior to study entry, **as defined as “Symptoms of influenza-like illness as well as a proven history, by RT-PCR, of novel influenza H1N1 infection, or, has**

**positive influenza diagnostic testing since June 2009 (specificity to H1N1 not required) prior to study entry.”**

- 4.24 Has received any live licensed vaccine within 4 weeks, or inactivated licensed vaccine within 2 weeks, prior to study entry.
- 4.25 Has received a non-licensed agent (vaccine, drug, biologic, device, blood product, or medication) within 4 weeks prior to study entry, or expects to receive another non-licensed agent during the course of the study.
- 4.26 Has an acute illness and/or a documented temperature greater than or equal to 100.0°F within 24 hours prior to study entry.
- 4.27 Use of anti-cancer chemotherapy or radiation therapy within the 36 months preceding study entry, or has immunosuppression as a result of an underlying illness or treatment (other than HIV-1 infection).
- 4.28 Has an active neoplastic disease.
- 4.29 Long term use of glucocorticoids, including oral or parenteral prednisone or equivalent ( $\geq 2$  mg/kg per day or  $\geq 20$  mg total dose) for more than 2 weeks in the past 6 months, or high-dose inhaled steroids ( $>800$  mcg/day of beclomethasone dipropionate or equivalent) within the preceding 6 months (nasal and topical steroids are allowed).
- 4.210 Has received immunoglobulin or other blood products within the 3 months prior to study entry.
- 4.211 History of Guillain-Barré Syndrome in the subject or subject's family (parents, siblings, half siblings, or children).
- 4.212 Onset of a neurological disorder including (but not limited to) absent ankle and patellar deep tendon reflexes in both legs (all four absent) within the past 6 months.
- 4.213 Disproportionate loss of strength in lower extremity or extremities, compared to the upper extremities within the past 6 months.
- 4.214 Has any condition that would, in the opinion of the site investigator, place the subject at an unacceptable risk of injury or render the subject unable to meet the requirements of the protocol.

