## SUMMARY OF CHANGES

All changes in this version appear in boldface type. Editorial changes including corrections of typographical errors and other changes required to update information that does not affect regulatory issues or patient consent may also be included. These changes contain all the information contained in Letter of Amendment #1, dated 10/13/09:

1. The Influenza A (H1N1) 2009 Monovalent Vaccine manufactured by Novartis has been approved by the FDA. All references to the study product have been modified to indicate that the study vaccine is a licensed product and is no longer considered as investigational.
2. The vaccine is now referred to as “Influenza A (H1N1) 2009 Monovalent Vaccine” throughout the protocol. The virus is now referred to as “2009 H1N1 Influenza A virus” throughout the protocol. Similarly, all references to ‘S-OIV’ or ‘swine-origin’ have been removed.
3. The Table of Contents has been updated.
4. Schema and Section 2.2 – Secondary Objectives. An additional secondary objective has been added: “To explore factors related to HIV and its treatment that might affect the responses to H1N1 vaccinations.”
5. Section 4.2 – Exclusion Criteria; Informed Consent: The Influenza A (H1N1) 2009 Monovalent Vaccine (Novartis) does not contain any of the following allergens: Gelatin, formaldehyde, octoxinol or chicken protein, but does contain neomycin and polymyxin. Therefore, exclusion criterion 4.21 has been updated to: “Has a known allergy to eggs, egg products, neomycin or polymyxin.”
6. Section 4.23 – Exclusion Criteria: This is has been expanded to include a definition of H1N1 infection, and as such now reads: “Has a history of probable or proven pandemic 2009 H1N1 Influenza A infection prior to study entry, as defined as “Symptoms of influenza-like illness as well as a proven history, by RT-PCR, of novel influenza H1N1 infection, or, has positive influenza diagnostic testing since June 2009 (specificity to H1N1 not required) prior to study entry.”
7. Section 4.7: Enrollment procedures have been updated.
8. Section 5.12; Needle Length Chart: It is recommended that all subjects in P1088 should have study vaccine administered in the deltoid muscle. Vaccinations with study vaccine that are to be administered in the lateral thigh should follow the instructions in the package insert.

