**22. WHAT OTHER CHOICES DO I HAVE BESIDES THIS STUDY?**

(IC page 8/10)

Text has been modified to read:

“Alternatives to your participation in this study include receiving from your health care provider the seasonal flu vaccine and Influenza A (H1N1) 2009 Monovalent Vaccine. Alternatively, you may choose not to receive any vaccine.”

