This study will assess the safety and immune response following each of the two doses of Novartis **Influenza A (H1N1) 2009 monovalent vaccine** in HIV-1 infected children and youth in the US and Puerto Rico. Two doses are thought to be required because study subjects have had no prior exposure to **2009 H1N1 Influenza A**. Because seasonal influenza vaccine often results in blunted response in HIV-1 infected persons, we have opted to investigate the higher dose of antigen, 30mcg, in comparison to the 15mcg dose that is currently being studied in ongoing trials of the **Influenza A (H1N1) 2009 monovalent vaccine** in healthy children. We have also opted to stratify our study population into 3 groups based on age. The groups were selected to provide information across all age groups and with knowledge that there would be insufficient power to compare immune response across age groups. This study is limited to HIV-1 perinatally infected children and youth.

In order to understand the mechanism of disease and protection, we will investigate the seroresponse, duration of response, and development of influenza-like illness following vaccine in this population. We also propose investigation of the cell-mediated response to vaccine. The generation of cytotoxic T lymphocyte (CTL) responses against **2009 H1N1 Influenza A** is of particular interest, because this virus replicates better in lung tissue than seasonal influenza and CTLs are the major mediator of viral clearance in the lungs. Memory B cells to **2009 H1N1 Influenza A** will ensure that the host responds adequately to exposure to the wild type virus.

In summary, **2009 H1N1 Influenza A** is likely to infect a significant proportion of HIV-1 infected children and youth if an effective vaccine is not available

before infection is widespread. Infection will likely lead to severe disease in this vulnerable population, therefore, vaccine efforts are critical. Immunogenicity of the candidate **Influenza A (H1N1) 2009 monovalent vaccine** must be established in HIV-1 infected children in order to assure that this population is protected. Lack of a protective immune response would support the need for additional measures to protect this high risk population.

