4.4 Exclusion Criteria for STEP II

If a subject meets any of the following exclusion criteria, they should not receive Dose #2 (see section 6.4).

- 4.41 Has received a non-licensed agent (vaccine, drug, biologic, device, blood product, or medication), other than from participation in this study, since Dose #1, or expects to receive another non-licensed agent before the end of the study.
- 4.42 Use of anti-cancer chemotherapy or radiation therapy since Dose #1, new diagnosis of an active malignancy, or is immunosuppressed as a result of an underlying illness (other than HIV-1 infection) or treatment.
- 4.43 Use of glucocorticoids, including oral or parenteral steroids ( $\geq 2$  mg/kg per day or  $\geq 20$  mg total dose) for more than 2 weeks since vaccine Dose #1, or high-dose inhaled steroids ( $>800$  mcg/day of beclomethasone dipropionate or equivalent) since Dose #1 (nasal and topical steroids are allowed).
- 4.44 Has received immunoglobulin or other blood products since Dose #1.
- 4.45 Any Grade 3 toxicity or adverse event experienced by a subject unless the investigator has received protocol team approval.

- 4.46 Any Grade 4 toxicity or adverse event (other than injection site reaction or fever) that is definitely, probably or possibly related to study vaccine.
- 4.47 Any Grade 4 injection site reactions or fever experienced by a subject, unless the investigator has received protocol team approval.
- 4.48 Any Grade 4 adverse events that are definitely not or probably not related to study vaccine, unless the investigator has received protocol team approval.
- 4.49 New occurrence or new awareness of Guillain-Barré Syndrome in the subject or subject's family (parents, siblings, half siblings, or children) since Dose #1.
- 4.410 A new onset of a neurological disorder including (but not limited to) absent ankle and patellar deep tendon reflexes in both legs (all four absent) since Dose #1.
- 4.411 Disproportionate loss of strength in lower extremity or extremities, compared to the upper extremities (not thought to be related to pregnancy) since Dose #1.
- 4.412 Documented **2009 H1N1 Influenza A infection** since Dose #1 (see 4.23 for definition)
- 4.413 The subject, parent, or guardian refuses further vaccination.
- 4.414 Any new disease which the investigator judges to be clinically significant or clinically significant findings since Dose #1 that, in the investigator's opinion, would compromise the safety of the subject.

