#### 4.51 Vaccines

Receipt of any vaccines besides the study product will be collected throughout the study from enrollment to the off study visit. The administration of inactivated licensed vaccines, including inactivated seasonal influenza TIV, should be at least

2 weeks (14 days) before Dose #1 or delayed until the STEP II Day 10 visit has occurred and immunogenicity samples have been collected.

The administration of live licensed vaccines, including seasonal cold-adapted live influenza vaccine, should be at least 4 weeks (28 days) before Dose #1 or delayed until at least the STEP II Day 10 visit has occurred and immunogenicity samples have been collected.

If administration of the seasonal influenza vaccine outside of the windows described above is necessary for clinical care, the investigator should notify the protocol team at [[contact]](mailto:[contact]). The seasonal influenza vaccine is not provided by this study.

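### Beyond a 2- or 4-week wash-out, no entry or evaluability rule deals with earlier receipt of a licensed 2009 H1N1 vaccine, so already-primed subjects can enter the primary response proportions

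*Combined protocol and SAP*

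**What the plan says.** **Rationale.** Section 1.22 gives the reason for the schedule: "Two doses are thought to be required because study subjects have had no prior exposure to" 2009 H1N1 Influenza A. The same section says children and young adults have no protective titres.

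**Entry criteria.**
- 4.23 deals with infection: "Has a history of probable or proven pandemic" 2009 H1N1 infection is an exclusion.
- 4.24 is a wash-out for licensed vaccines: "Has received any live licensed vaccine within 4 weeks, or inactivated licensed vaccine within 2 weeks, prior to study entry".
- 4.25 covers only unlicensed products: "Has received a non-licensed agent (vaccine, drug, biologic, device, blood product, or medication) within 4 weeks prior to study entry".

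**Between doses.** 4.412 again addresses infection. 4.41 again addresses unlicensed products: "Has received a non-licensed agent (vaccine, drug, biologic, device, blood product, or medication), other than from participation in this study, since Dose #1". Section 4.51 asks that inactivated licensed vaccines be given no later than "2 weeks (14 days) before Dose #1 or delayed until the STEP II Day 10 visit has occurred and immunogenicity samples have been collected".

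**Status of the product.** Item 1 of the Summary of Changes says that "the study vaccine is a licensed product and is no longer considered as investigational". Item 22 gives the consent wording: "Alternatives to your participation in this study include receiving from your health care provider the seasonal flu vaccine and Influenza A (H1N1) 2009 Monovalent Vaccine".

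**Endpoint and analysis.** 8.214 defines response as HAI at or above 1:40, 21 days after Dose #1 and 10 days after Dose #2. It does not require a baseline titre below 1:40 or a fold rise. 8.612 reports the proportion with a 90% interval and reads the lower limit as a 95% confidence bound. The evaluable definition in 8.4 requires two study doses 21–28 days apart and HAI samples in window, and nothing about vaccine history.

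**Data collected.** Baseline HAI is drawn at screening. Footnote 2 of Appendix IA asks for vaccinations in the 2009–2010 seasonal influenza vaccine periods through the end of the study.

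**The concern.** The plan protects naivety to 2009 H1N1 against one route of exposure, infection, and is silent on the other, vaccination. The silence began to matter when the product was licensed. Before that, an H1N1 vaccine given outside the study was an unlicensed agent, and 4.25 and 4.41 reached it. Now only the short general wash-out does.

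In a single-arm study there is no comparator to expose the consequence. For a subject vaccinated before entry, the sample labelled as post-Dose #1 follows a second or later antigen exposure. An absolute threshold cannot separate titre already present, or a recall response, from response to the study dose. A baseline titre helps only in part, because a primed subject can sit below 1:40 at entry.

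At stake is the meaning of the two primary response proportions, which are meant to describe what one and two study doses achieve in this population.

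**Working it through.** **1. Which rule reaches an H1N1 vaccine given before entry?**

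| Earlier exposure | Rule that applies | Result |
|---|---|---|
| 2009 H1N1 infection | 4.23 | Excluded |
| Unlicensed vaccine within 4 weeks | 4.25 | Excluded |
| Licensed inactivated H1N1 vaccine within 2 weeks | 4.24 | Excluded |
| Licensed live H1N1 vaccine within 4 weeks | 4.24 | Excluded |
| Licensed inactivated H1N1 vaccine more than 2 weeks before | None | Eligible |
| Licensed live H1N1 vaccine more than 4 weeks before | None | Eligible |

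The discretionary criterion 4.214 concerns risk of injury or inability to meet protocol requirements, so it does not fill the last two rows.

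**2. Does anything later in the plan remove these subjects?** The evaluable definition (8.4), the endpoint (8.214) and the primary analysis (8.612) carry no condition on vaccine history or baseline titre. Baseline titre is used only for secondary objective 1. The predictors listed in 8.62 do not name earlier H1N1 vaccination.

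**3. The plan's own precision.** Exact (Clopper–Pearson) 90% limits for N=120 reproduce Table 3:
- 90/120 = 75%: 67.65% to 81.39% (Table 3: 68% to 81%)
- 60/120 = 50%: 42.14% to 57.86% (Table 3: 42% to 58%)

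The half-width at 50% is (57.86 − 42.14)/2 = 7.86 points, or about 8.

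**4. Size of the bias.** Let p be the share previously vaccinated, v their proportion at or above 1:40, and r the naive proportion. The observed proportion is (1 − p)r + pv, so

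bias = p × (v − r).

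The documents give none of these three values. Assumed ranges: p 5–20%, v 90–100%, r 50–70%.
- Smallest: 0.05 × (0.90 − 0.70) = 1.0 point
- Largest: 0.20 × (1.00 − 0.50) = 10.0 points

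With r = 50% and v = 100%:

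| Previously vaccinated, of 120 | Expected responders | Observed | Exact 90% interval |
|---|---|---|---|
| 0 | 60 | 50.0% | 42.1–57.9 |
| 6 (5%) | 63 | 52.5% | 44.6–60.3 |
| 12 (10%) | 66 | 55.0% | 47.1–62.7 |
| 24 (20%) | 72 | 60.0% | 52.1–67.5 |

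**5. When does the bias exceed the half-width?** With r = 50%, it needs p > 7.86/(100v − 50). For v = 100% that is 7.86/50 = 15.7%, or 19 of 120. For v = 80% it is 7.86/30 = 26.2%, or 32 of 120.

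**6. Effect of leaving such subjects out.** Take the plan's own example of 90/120 and suppose that 6, 12 or 24 of the responders had been vaccinated earlier:
- 84/114 = 73.7% (66.0–80.4)
- 78/108 = 72.2% (64.3–79.2)
- 66/96 = 68.8% (60.1–76.5)

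Keeping them gives 75.0% (67.7–81.4).

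**The case against.** The other side has real strength.

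- **Recent doses are barred.** A reader might infer that nothing at all keeps out an H1N1 vaccinee. That is not so: 4.24 excludes an inactivated dose in the last two weeks and a live dose in the last four. Between doses, 4.51 defers licensed vaccines until the Step II Day 10 samples are drawn. The gap is confined mainly to an older dose before entry.
- **The stated premise names the virus.** Section 1.22 speaks of exposure to 2009 H1N1 Influenza A and does not say that subjects are vaccine-naive. Extending it to vaccine antigen is an inference. It is a fair one, since the argument for two doses is immunological naivety.
- **Occurrence is not documented.** The consent wording shows that the vaccine was an alternative to taking part, not that candidates had already received it. Planned accrual was only 4–6 weeks. The share could be near zero.
- **The larger figures need generous assumptions.** The protocol expects blunted influenza vaccine responses in this population, so 100% of earlier vaccinees at or above 1:40 is an upper bound. At 5–10% previously vaccinated and a naive response of 50%, even that bound gives 2.5–5 points, inside the half-width.
- **The analysis is descriptive.** There is no success threshold to be crossed wrongly, and baseline HAI and vaccine history are collected.

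All of this limits the size and likelihood of the problem. It does not close the gap, because no rule in the plan uses the collected history, and without such a rule the report could not show that the share was negligible.

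**Conclusion.** The gap in the text is certain; its consequence is not. Following the plan exactly, a subject given an inactivated licensed 2009 H1N1 vaccine more than two weeks before entry is counted with naive subjects in both primary response proportions. Wherever such subjects respond more often than naive ones, the bias is upward. Under the assumed ranges it is 1 to 10 points, and it exceeds the half-width of about 8 points only if roughly 16% or more were previously vaccinated, taking a naive response of 50% and every earlier vaccinee at or above 1:40. With no earlier vaccinees it is zero.

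A reader might conclude that the primary estimates are invalid or would fall outside their interval. The documents do not support that, because they give neither the share vaccinated nor the response in those subjects.

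A minor secondary point follows from 4.51. A non-study H1N1 dose after Step II Day 10 is not ruled out, so a 6-month titre (8.221, 8.231) could reflect a booster rather than persistence. Nothing suggests that this would be common.

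This is a should-fix: a cheap improvement that protects how the primary immunogenicity result is read.

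**What to change.** 1. **Section 4.2:** add an exclusion for receipt of any 2009 H1N1 vaccine, licensed or not, before study entry.
2. **Sections 8.4 (evaluable definition) and 8.612:** state that subjects with a recorded non-study 2009 H1N1 vaccine before the relevant HAI sample are left out of the primary immunogenicity proportions. This belongs in the analysis text and not in 4.4, where it would read as a bar on Dose #2. No change to the Dose #2 rules is proposed.
3. **Subjects already enrolled:** report both primary proportions with and without those who had an earlier H1N1 vaccine, using the vaccination history in Appendix IA footnote 2. First confirm that this history captures H1N1 vaccine. The footnote refers to the seasonal vaccine periods, and the collection window in 4.5 goes back only 28 days before entry.
4. **Sections 8.221 and 8.231:** report 6-month results without titres drawn after a recorded non-study H1N1 vaccine.

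The cost is one eligibility line and a few sentences of analysis text. No new data are needed if the history check in item 3 succeeds. A few candidates become ineligible, the evaluable N may be slightly smaller, and a few 6-month titres may be dropped.
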